### ***Timing of outcome assessment***

**Protocol:** Patients were examined at two time points; at baseline and 14-16 weeks after treatment initiation, where primary endpoints are evaluated.

**SAP:** Outcome assessment was scheduled to be 14-16 weeks after treatment initiation but a window of +/- 4 weeks are allowed.

**Rationale:** Taking the COVID-19 pandemic into account, we have decided to allow a window of +/- 4 weeks for outcome assessment at the follow-up visit in order to prevent a large number of missing outcomes.

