### 6.3. Missing data

As previously stated (under section 4.3), the primary analyses will be based on the ITT population. Accordingly, participants will be followed up, assessed and analyzed as members of their initial dietary group, irrespective of their adherence to the planned course of treatment with biological agents and potential personal changes in dietary habits (i.e., independent of withdrawals and cross-over phenomena). Every effort will be made to minimize missing data (i.e. both baseline covariates [ $X$ 's] and outcome data [ $Y$ 's]). Loss to follow-up and missing data for various reasons is however difficult to avoid in pragmatic, real-world observational studies, from clinical practice.

We will apply the analysis framework suggested by White et al (2011) in which missing data related to the ITT approach depend on making plausible assumptions about the missingness of the data and including all participants in subsequent sensitivity analyses [24]:

**#1. Attempt to follow up all participants who signed informed consent**, even if they withdrew from allocated treatment or significantly modified their dietary habits (i.e., we contact all individuals unless they explicitly stated that they had withdrawn their consent).

**#2. Perform a main analysis of all observed data that are valid under a plausible assumption.** For our primary analyses we will assume that data is 'Missing At Random' (MAR). The MAR assumption requires that, conditional on the observed data for the case,  $Y_{obs}$ , the probability that a value is missing does not depend on the true values of the missing items,  $Y_{mis}$ . Multiple imputation (MI) will be used to account for participants from whom we have an answered FFQ (i.e. the ITT population) but potentially with missing outcome information at follow-up.

**#3. Perform sensitivity analyses.** In order to explore the effect of departures from the assumption made in the main analysis (#2) other analysis techniques will be applied; these models will potentially be informative even if data are 'Missing Not At Random' [MNAR].

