**Use and reporting of analyses using multiple imputation.** When we assume data are missing at random (MAR), then unbiased and statistically more powerful analyses is possible by building a more general model based on multiple imputation. Multiple imputation (MI) is a general approach to the problem of missing data that allow for the uncertainty about the missing data by creating several different plausible imputed data sets and appropriately combining results obtained from each of them.

The MI first stage will be to create multiple (i.e. at least 5) copies of the dataset, with the missing values replaced by imputed values. These will be sampled from their predictive distribution based on the observed data.

The MI second stage will be to use standard statistical methods to fit the logistic regression model of interest to each of the imputed datasets; variables included in the imputation models will be listed. At least five imputed datasets will be created. Estimated associations (i.e.  $\ln[OR_i]$ ) in each of the imputed datasets will differ

because of the variation introduced in the imputation of the missing values, and they are only useful when averaged together to give overall estimated associations. Standard errors will be calculated using Rubin's rules [51] which take account of the variability in results between the imputed datasets, reflecting the uncertainty associated with the missing values. Valid inferences are obtained because we will be averaging over the distribution of the missing data given the observed data.

We will report the number of missing values for each variable of interest, and the number of cases with complete data for each important component of the analysis. We will provide reasons for missing values if possible and indicate how many individuals were excluded because of missing data when reporting the flow of participants through the study (Figure 1). We will provide explicit reasons for missing data for the primary outcome measure in terms of other variables and explore whether there are differences between individuals with complete and incomplete primary outcome data, by performing logistic regression analyses with "missingness" being the dependent variable ( $Y_{\text{Mis}}$  vs.  $Y_{\text{Obs}}$ ) and various baseline characteristics (covariates) as independent variables.

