The selection of the variables to be used in the imputation of missing data will follow the following three basic rules, that will enable us to perform multiple imputation and analysis that is statistically robust:

1. Include all the key analysis variables, regardless of whether they have missing data;
2. Include other variables that are correlated or associated with the primary outcome we intend to analyze (regardless of whether these variables will ultimately be included in our analysis);
3. Include variables that predict item missing data on the analysis variables (again regardless of whether these variables will ultimately enter our analysis).

We will report the details of the software used and of key settings for the imputation modeling; incl. the number of imputed datasets that were created. We will use mainly default options but do specify a specific SEED value (e.g. the specific date of the analysis); this seed will be used to initiate the generation of random numbers that are used in the imputation process. The specification of a fixed SEED value enables us to exactly replicate the random number generation sequence and reproduce the results of a multiple imputation analysis run. We will use the following default settings: M=5 repetitions and 20 burn-in iterations.

Since our analytic objective is to estimate the Odds Ratios (from logistic regression) of clinical response depending on the dietary group (and other covariates simultaneously), we will use logistic regression with a "BY statement" to execute five separate logistic regressions, one for each imputation repetition data set contained in the corresponding "MI data set".

The MI third and final step in our analysis plan is to combine these five sets of regression estimates to produce the final MI estimates of the logistic regression model parameters, their standard errors, and 95% CIs for the true parameter values. As a consequence, the parameter estimates from the five individual logistic regressions are averaged and the associated standard errors account for the imputation variability.

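### The primary multiple-imputation analysis is run with only five imputations, so a P value near 0.05 depends materially on the random seed

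*SAP*

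**What the plan says.** SAP section 6.3 applies multiple imputation to ITT participants who answered the FFQ but lack follow-up outcome data, under this assumption: "For our primary analyses we will assume that data is 'Missing At Random' (MAR". For pooling it says "Standard errors will be calculated using Rubin's rules".

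The number of imputations is given in two ways. The description of the first two stages sets a minimum of five twice, the second time as "At least five imputed datasets will be created". The later text on software settings says "We will use the following default settings: M=5 repetitions and 20 burn-in iterations". The steps that follow count to five: the analyst is "to execute five separate logistic regressions, one for each imputation repetition data set", and then to "combine these five sets of regression estimates to produce the final MI estimates". Five is therefore what would be run, although the stated minimum would permit more.

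On the seed, the plan is to "do specify a specific SEED value (e.g. the specific date of the analysis". No value is written down. The stated reason for a seed is that a run can be replicated exactly.

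Section 6.3 sets no target for Monte Carlo error and no rule linking M to the amount of missing data. Neither the four sensitivity analyses listed in section 6.4 nor its best-case and worst-case scenarios vary M or the seed.

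**The concern.** Each imputation adds random draws, and averaging over M of them leaves residual Monte Carlo noise in the pooled log odds ratio and in its estimated variance. With M = 5 the between-imputation variance is estimated on only four degrees of freedom. If the noise is large relative to the standard error, two analysts with the same data, model and code but different seeds can report P values on opposite sides of 0.05 for the primary outcome.

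Two features of the plan add to this. The minimum-of-five wording allows M to be settled after results are visible, and the seed is chosen only when the analysis is run. Section 3.2 also records that recruitment ended before the planned 320 patients. That lowers power and makes a borderline result more plausible under the planned effect.

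**Working it through.** **The plan's own figure.** Section 3.2 gives power 0.924 for a total of 318, a 1:2 split, and response of 60% against 40%. With 106 and 212 patients:

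- Pooled proportion = (106 × 0.6 + 212 × 0.4)/318 = 0.4667.
- Null standard error = √[0.4667 × 0.5333 × (1/106 + 1/212)] = 0.0593.
- Alternative standard error = √(0.24/106 + 0.24/212) = 0.0583.
- Power = Φ[(0.2 − 1.96 × 0.0593)/0.0583] = 0.924. The SAP's figure reproduces.

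**Inputs.** From the SAP: M = 5, Rubin's rules, two-sided 0.05. Assumed, because no missing rate is given: a fraction of missing information g of 0.05, 0.1, 0.2 or 0.3.

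**Formulas.** Hold the data fixed and let only the imputation draws vary. Scale so that the total variance with unlimited imputations is 1: within-imputation variance W = 1 − g, between-imputation variance B = g. Then:

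- Monte Carlo SE of the pooled estimate, as a share of its SE: √(g/M).
- Rubin's total variance: T = W + (1 + 1/M)B.
- Degrees of freedom: (M − 1)[1 + W/((1 + 1/M)B)]².

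**One case by hand, g = 0.2, M = 5.** Monte Carlo share = √(0.2/5) = 0.20. T = 0.8 + 1.2 × 0.2 = 1.04. Degrees of freedom = 4 × (1 + 0.8/0.24)² = 75. If the unlimited-M z is 1.96, the middle 90% of seeds move z by ±1.645 × 0.20 = ±0.33, from 1.63 to 2.29. That alone spreads P over roughly 0.02 to 0.10. Letting the estimated B vary as well widens the upper end, as the table shows.

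**All cases.** The pooled estimate is drawn from a normal distribution with variance B/M, the estimated B from B·χ²(M−1)/(M−1), and P from the t reference; 400,000 draws per cell.

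| g | Monte Carlo share, M = 5 | 5th–95th percentile of P, unlimited-M P = 0.05: M = 5 | same, M = 100 | Seeds with P ≥ 0.05, unlimited-M P = 0.04: M = 5 | same, M = 100 |
|---|---|---|---|---|---|
| 0.05 | 10% | 0.034–0.077 | 0.046–0.055 | 22% | 0% |
| 0.1 | 14% | 0.028–0.095 | 0.044–0.057 | 34% | 0.4% |
| 0.2 | 20% | 0.020–0.134 | 0.041–0.061 | 44% | 4% |
| 0.3 | 24% | 0.015–0.173 | 0.038–0.065 | 49% | 10% |

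The 0.05 columns show spread only. A limiting P of exactly 0.05 puts about half the seeds on each side whatever M is, so the 0.04 columns are the fair measure of crossing.

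**Further from the threshold.** With M = 5 and g from 0.05 to 0.3, the share of seeds crossing 0.05 is 4% to 38% for an unlimited-M P of 0.03, and 20% to 32% for 0.06. For P = 0.01 it is 0% to 0.1% at g up to 0.1, rising to 4% at 0.2 and 11% at 0.3.

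**Direct check.** Missing binary outcomes were imputed at 106 against 212 patients with a group-only logistic model. With 10% missing and a complete-case P of 0.041, the 95% range of P over 20,000 seeds was 0.019 to 0.091 at M = 5, with 35% of seeds at 0.05 or above. At M = 100 it was 0.035 to 0.048, with under 1%. This check omits covariates.

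**The case against.** Several points on the other side are sound.

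- **Validity.** Rubin's rules allow for finite M through the 1 + 1/M term and the t reference, so inference at M = 5 is valid on average. The loss of precision is small: the nominal 95% interval is about 1.4% wider than with unlimited imputations at g = 0.1, 4% at 0.2 and 7% at 0.3. This stands. A reader might infer that five imputations bias the result or invalidate the test; they do not.
- **Amount of missing data.** A reader might infer that the SAP expects many missing outcomes. It does not say so. The wider assessment window in section 4.2 is there "in order to prevent a large number of missing outcomes", and UC patients without endoscopy keep a primary outcome through the partial Mayo index. Section 6.3 says only that some missing data are hard to avoid. The auxiliary variables required in the imputation model may also lower g. Hence the assumed range starts at 0.05.
- **Seed.** A reader might infer that repeating the analysis on another day would change the answer. It would not if the recorded seed is reused, and section 6.5 promises the source code. The date is only an example. What stands is narrower: no number is fixed before the analysis.
- **Other safeguards.** The complete-case analysis does not depend on a seed, the SAP commits to reporting the number of imputations, and section 3.2 places the study within exploratory prognostic research. These reduce the weight of a crossing but do not stabilise the primary P value.
- **Choice of 100.** This is partly preference. At g = 0.1, M = 20 already narrows the 5th–95th percentile range to 0.037–0.068.

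**Conclusion.** The point holds as one of seed-dependent instability in the primary result, together with two inconsistent statements of M. It matters when P is near 0.05: at an unlimited-M P of 0.04, between 22% and 49% of seeds would report 0.05 or more with M = 5, against 0% to 10% with M = 100. It is negligible for a clear result with little missing information (P = 0.01, g up to 0.1).

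The size rests on an assumed g of 0.05 to 0.3, since the SAP gives no missing rate, and on the normal approximation for the log odds ratio. Even the lowest assumed value leaves a visible effect. The change is worth making because it removes most of the instability at almost no cost, not because the current plan is invalid.

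**What to change.** In section 6.3, replace both the minimum-of-five wording and the setting of five with a single larger number, for example M = 100. If a smaller number is preferred, it should be no lower than the percentage of incomplete cases. Change the counts of regressions and of combined estimates to match.

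Write the numeric seed into the SAP before analysis. This removes discretion over the seed but does not reduce Monte Carlo error; the larger M does that.

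Report the Monte Carlo error of the log odds ratio and of the P value with the primary result, since at g = 0.3 some dependence on the seed remains even with M = 100.

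The cost is a few edited sentences and minutes of computing time. No data collection, outcome definition or model changes.

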## 6.4. Sensitivity analyses

Where complete cases and multiple imputation analyses give different results, the analyst should attempt to understand why, and this should be reported in publications [52]. Robustness is a concept that refers to the sensitivity of the overall conclusions to various limitations of the data, assumptions, and analytic approaches to data analysis. Robustness implies that the treatment effect and primary conclusions of the trial are not

substantially affected when analyses are carried out based on alternative assumptions or analytic approaches. For the purpose of sensitivity, multiple sensitivity analyses will be performed to assess the robustness of the primary analyses. For instance, a simplistic 'single step, null responder imputation' would represent a conservative base case and is potentially valid even if data is 'missing not at random' as it assumes and implies that patients have not improved or worsened after entering the study. When there are missing outcome data for our dichotomous outcomes we will explore "best" and "worst" case scenarios by replacing missing values with "good" outcomes in one group and "bad" outcomes in the other group. Sensitivity analyses will include analyses based on:

- 1) complete case analysis,
- 2) a 'non-responder-imputation',
- 3) the 'per protocol population',
- 4) the population meeting the unmodified eligibility criteria  
(exclusion of patients initiating treatment with biologics targeting other agents than TNF and patients previously treated with biologics).

Results of the sensitivity analyses are presented in the Appendix, table 2. When the different sensitivity analyses are in agreement, and the analyses on the sensitivity analyses and the main analysis lead to essentially the same conclusions, confidence in the trial results is increased.

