### 3.2. Sample size and power considerations

Deciding on sample size is a well-known difficulty with exploratory prognostic factor research studies. To obtain an adequate number of outcome events, we applied 'the rule of thumb', whereby 10 outcomes are needed for

each independent variable. We planned to enroll 320 patients in total with the anticipation that 50% of these would experience a clinical response within the 14–16 weeks period after initiation of biological therapy. With this in mind and anticipating that we would observe at least 160 events (i.e., clinical response among the 320 patients), the study would be sufficiently powered to explore the impact of as many as 16 independent variables including condition and clinical center. Since using the ‘rule of thumb’ method to justify sample size is a debated practice, we went one step further and estimated the statistical power to detect differences between two dietary groups. For the contrast between groups and for a comparison of two independent binomial proportions (those with high-fiber, low-meat intake vs. other) using Pearson’s  $\chi^2$  statistic, with a  $\chi^2$  approximation, with a two-sided significance level of 0.05 ( $P < 0.05$ ), a total sample size of 318—assuming an ‘allocation ratio’ of 1 to 2 (one-third)—has an approximate power of 0.924 (i.e., >90% statistical power) if the anticipated proportions responding to therapy are 60% and 40%, respectively. However, due to pre-specified time constraints, inclusion to BELIEVE was terminated on 03-30-2020 before reaching the planned sample size of 320 patients in total.

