#### 6.1.4. Exposure and confounding variables

##### **Exposure variable**

We will stratify the patients in BELIEVE into two groups (exposed versus unexposed) based on the ratio of fiber to meat intake (FtM [grams per day]):

$$FtM = \frac{\text{Fibers}}{\text{Red and processed meat}},$$

which will be calculated from the food frequency questionnaire (FFQ) administered to the patients at baseline. From this ratio, exposure is defined as the upper 33.3% of the total study sample (called the high fiber low meat group, HFLM) leaving the lower 66.6% of the sample as those un-exposed (low fiber high meat, LFHM).

Secondary explorative analysis will include defining exposure as 1) the upper 33.3% (high fiber; HF) of the study sample with respect to intake of dietary fibers (versus the lower 66.6% [low fiber; LF], and 2) the lower 33.3% (low meat; LM) of the study sample with regard to red/processed meat intake (versus the upper 66.6% [high meat; HM]).

The FFQ used in the present study was developed and validated in relation to the 2007-2008 Danish Health Examination Survey [47]. It was internet-based and administered to the participants prior to initiation of biological therapy with questions covering the habitual dietary intake during the past month. The FFQ contained information from 267 different food groups. For each item, frequency of consumption was evaluated by eight categories ranging from “newer/seldom” to “twice or more per day”. In order to quantify portion sizes for main meals and other main food items, a photographic food atlas consisting of different food and meal series was included at the end of the questionnaire. However, fixed portion sizes were used for some food items with more standardized portion sizes such as fruits. The actual weight in grams for each food item will be derived by multiplying the reported frequency of consumption with estimated portion sizes. Total energy intake and intake of different nutrients will be quantified using the Danish Food Composition Tables (National Food Institute, Technical University of Denmark, <https://frida.fooddata.dk/>).

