Appendix Table 2. Sensitivity analyses of the comparison of HFLM versus LFHM.

| Outcome                                                                                                                                                                                                                                                                                                                                                                                                                                                                                                                                                | Complete-case analysis |      |                     | Non-responder imputation analyses |                     |          | Per protocol population |          |                     | Unmodified eligibility criteria |                     |          |
|--------------------------------------------------------------------------------------------------------------------------------------------------------------------------------------------------------------------------------------------------------------------------------------------------------------------------------------------------------------------------------------------------------------------------------------------------------------------------------------------------------------------------------------------------------|------------------------|------|---------------------|-----------------------------------|---------------------|----------|-------------------------|----------|---------------------|---------------------------------|---------------------|----------|
|                                                                                                                                                                                                                                                                                                                                                                                                                                                                                                                                                        | HFLM                   | LFHM | Difference (95% CI) | P value*                          | Difference (95% CI) | P value* | Difference (95% CI)     | P value* | Difference (95% CI) | P value*                        | Difference (95% CI) | P value* |

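### Non-responder imputation is called conservative, but that holds only for each diet group's response rate, not for the HFLM–LFHM contrast unless missingness is similar in both groups

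*SAP*

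**What the plan says.** The primary analysis is multiple imputation under missing at random (SAP 6.3). Section 6.3 then promises sensitivity analyses by other techniques and says of them that "these models will potentially be informative even if data are 'Missing Not At Random' [MNAR". Section 6.4 offers a single-step null-responder imputation as its example and says that it "would represent a conservative base case and is potentially valid even if data is 'missing not at random". The reason given is that it takes patients as neither improved nor worsened since entry. Validity is hedged; the word conservative is not, and nothing ties it to similar missingness in the two diet groups.

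Non-responder imputation (NRI below) is item 2 of the four numbered sensitivity analyses and has its own block in Appendix Table 2, "Non-responder imputation analyses". Section 6.4 also promises best- and worst-case scenarios for dichotomous outcomes, with favourable values imputed in one group and unfavourable values in the other. These appear neither in the numbered list nor in Appendix Table 2. The section closes by saying that agreement among the sensitivity analyses and with the main analysis raises confidence in the result.

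**The concern.** The study reports a contrast, the odds ratio of response for HFLM versus LFHM. Scoring every unassessed patient as a failure can only lower each group's response rate, and in that sense it is conservative. It has no fixed direction for the contrast, which moves towards whichever group was followed up better.

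Equal follow-up might be a reasonable working assumption in a randomised trial. Here section 6.1.4 itself accepts that exposure is not randomly allocated, and it names age, sex and smoking as possible confounders. Such factors could also affect attendance. If LFHM patients miss more visits, NRI shifts the odds ratio towards the study hypothesis and is no stress test of a positive main result. If HFLM patients miss more, NRI can mask a real association. A reader told that the analysis is conservative would not look for either.

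**Working it through.** **Inputs from the SAP.** Section 3.2 plans the power calculation "for a comparison of two independent binomial proportions", "with a two-sided significance level of 0.05", and "a total sample size of 318" with a one-to-two split. Section 6.1.4 matches this: "exposure is defined as the upper 33.3% of the total study sample". That gives 106 HFLM and 212 LFHM.

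**The plan's own figure.** Section 3.2 states that this design "has an approximate power of 0.924 (i.e., >90% statistical power) if the anticipated proportions responding to therapy are 60% and 40%, respectively".
- Pooled proportion: (106 × 0.60 + 212 × 0.40)/318 = 0.4667.
- SE under the null: √[0.4667 × 0.5333 × (1/106 + 1/212)] = 0.05935.
- SE under the alternative: √[0.24/106 + 0.24/212] = 0.05828.
- Power: Φ[(0.20 − 1.96 × 0.05935)/0.05828] = Φ(1.436) = 0.924. The stated figure is reproduced.

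**Assumptions, because the SAP gives no missing rates.** The missing share is m₁ in HFLM and m₂ in LFHM. Within each group missingness is unrelated to response. Under no diet effect both groups respond at r = 46.7%, the pooled rate above. The test is the same unadjusted two-proportion test.

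**Formula.** Under NRI the analysed proportion in group g is r_g(1 − m_g). With equal r the groups differ whenever m differs.

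**One case in full, 10%/20% missing.**
- Analysed rates: 0.4667 × 0.90 = 0.420 and 0.4667 × 0.80 = 0.373.
- Spurious odds ratio: (0.420/0.580)/(0.373/0.627) = 1.22.
- Pooled rate 0.389; SE₀ = 0.0580; SE₁ = 0.0583; difference 0.0467.
- Rejection favouring HFLM: 1 − Φ[(1.96 × 0.0580 − 0.0467)/0.0583] = 12.5%. Rejection favouring LFHM: 0.3%. Total 12.8%.

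**All cases with no diet effect, nominal 5%.** The three joint rates shown are from simulation; the other columns use the formula.

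| Missing HFLM/LFHM | Analysed rates | Odds ratio | NRI rejects | NRI and complete case both significant, same direction |
|---|---|---|---|---|
| 15%/15% | 39.7% / 39.7% | 1.00 | 5.0% | 3.4% |
| 10%/15% | 42.0% / 39.7% | 1.10 | 6.9% | – |
| 10%/20% | 42.0% / 37.3% | 1.22 | 12.8% | 2.8% |
| 10%/25% | 42.0% / 35.0% | 1.34 | 23.1% | – |
| 10%/30% | 42.0% / 32.7% | 1.49 | 37.5% | 2.5% |

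Simulated NRI rejection rates agree (37.8% in the last row). Complete-case analysis rejects about 5% in every row. Section 3.2 says that recruitment stopped short of target without giving the number. At an assumed 240 patients (80/160) the last three NRI rates are 10.9%, 18.7% and 29.8%.

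**Reverse direction.** Take a true 60% versus 40% with 25%/10% missing. The analysed rates are 0.60 × 0.75 = 45% and 0.40 × 0.90 = 36%. The odds ratio is (0.45/0.55)/(0.36/0.64) = 1.45, against a true (0.6/0.4)/(0.4/0.6) = 2.25. NRI power is about 34%. Complete-case power under the same missingness is about 86%. That is the fair comparator, since the 92% in section 3.2 assumes no missing data.

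**The case against.** The strongest defence is that NRI is one secondary analysis among several. The next sentence of section 6.4 promises group-specific best- and worst-case scenarios, which bound exactly this asymmetry. It would therefore be wrong to infer that NRI is the plan's only analysis aimed at data missing not at random. What stands against the plan is narrower: those scenarios have no place in the numbered list or in Appendix Table 2, and as extremes they do not show where between the two assumptions a conclusion would change.

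A reader might also infer that unequal follow-up would make NRI falsely confirm the main result. The documents and the figures do not support that. Section 6.4 draws confidence from agreement across analyses, not from NRI alone. Under no effect, joint significance of NRI and complete case does not rise with the gap (3.4% at equal missingness, 2.5–2.8% at gaps of 10 to 20 points). Most spurious NRI results would show up as discordance with complete case.

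Three further points stand as limits:
- If the missing patients really were non-responders, NRI would be right; the calculations assume the opposite.
- Every gap is assumed, and a 5-point gap does little harm.
- The calculations are unadjusted, whereas Appendix Table 2 adjusts as in the primary analysis.

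Some of the needed reporting is already planned: section 6.3 reports missing counts and models missingness on baseline characteristics, and the flow chart is split by dietary profile. None of this makes the unconditional word conservative correct for the contrast.

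**Conclusion.** The point holds as a wrongly stated property of a planned analysis. NRI is conservative for each group's response rate. For the HFLM–LFHM contrast it is not guaranteed to be, and its bias follows the difference in follow-up. Under the stated assumptions the false-positive rate ranges from 5% at equal missingness to 13% at a 10-point gap and about 38% at a 20-point gap; in the opposite direction power can fall to 34% where complete case keeps 86%. These figures show what could happen, not what did, since actual missingness is not in the SAP. The primary analysis is not affected, and neither false confirmation nor an absence of other analyses for data missing not at random can be claimed.

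**What to change.** In section 6.4, delete the description of NRI as a conservative base case. State instead that it counts a missing outcome as failure, and that it is conservative for the between-group contrast only if missingness is similar in both diet groups. Show the proportion with a missing primary outcome in HFLM and in LFHM beside the NRI result in Appendix Table 2.

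Add the best- and worst-case scenarios to the numbered list and to Appendix Table 2. Preferably add a group-specific delta-adjusted multiple imputation as well: multiply the imputed odds of response by a factor set separately in HFLM and LFHM, running from 1 (missing at random) towards 0 (NRI), and report the combination at which the primary conclusion changes.

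The cost is a wording change, a few extra runs of the imputation code already planned, and some additional table columns. No new data are needed.
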